### Study status

Currently the baseline data collection is ongoing.

## Discussion

Generalizability: To our knowledge, this is the first trial in India that will investigate the effectiveness of a self-help group led intervention in household where there is indoor smoking. The current study builds on a promising pilot trial which gave the proof of concept of this study.
^
30
^ Public engagement will continue to be central to this study which enhances the acceptability of the intervention and ensures sustainability.

As far as generalizability is concerned it will be generalizable to similar clusters and individuals inhabiting such clusters rather than to metropolitan areas.

The conceptual framework is the socioecological model which is important in understanding and determining behaviour change. As an implementation research, it seeks to assess impact by the RE-AIM framework (
Table 2). There is mounting interest in the use of theories, models and frameworks to gain insights into the mechanisms by which implementation is more likely to succeed.
^
48
^ Implementation research is intended to improve people’s health through informed policies, strengthened service delivery.
^
49
^ The implementation outcome variables are acceptability, adoption, appropriateness, feasibility, fidelity, coverage and sustainability. The large number of contextual factors that affect implementation can interact with each other and change over time which points to the fact that implementation occurs as part of complex adaptive systems.
^
48
^
^,^
^
49
^

**Table 2. T2:** The RE-AIM framework as applicable to KIFT.

RE-AIM dimension	Key questions
Reach	The smoker is expected to benefit. How many smokers were approached and how many were exposed to and benefited from intervention
Effectiveness	The key outcome is cotinine levels in the woman and or child living in the same house
Adoption	The program is applied in selected clusters called slums with the help of the self-help group members supported by frontline health worker-ASHA, elected representative, urban primary Health centre
Implementation	Consistency of delivery of intervention assessed by number of meetings conducted, one house to house visit to the smokers’ household, no of smokers household attended, content of message delivered including 3 A’s
Maintenance	In order to determine maintenance there will be an immediate survey after intervention and then another one at the end of 6 months

Though the RE-AIM network was developed to help make research findings more generalisable when developing and testing interventions, it also helps to plan strategies that can reach most people, effectively achieve and maintain positive health outcomes, be adopted in varied settings and be consistently implemented at a reasonable cost and be sustained in different kind of settings. At the end of the intervention, declaration meeting will be held where Mayor and other officials, elected representatives, health officials and press will attend. If the intervention is found to be successful, this will help in creating policies for smoke free homes.

*Ethical considerations*: Institutional Ethical Committee approval has been obtained vide letter dated 18-10-2022 of Amrita Institute of Medical Sciences
(IEC-AIMS-2022-COMM-284). Data collection will be done after getting informed consent and or assent. Assent will also be obtained from children above 11 years and parental consent from those below 11 years.

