^ PM < 10 μm enter the respiratory tract, but may be the result of mechanical processes such as construction activities, road dust resuspension and wind whereas PM < 2.5 μm (fine particles) originate primarily from combustion sources such as smoking.
^
34
^ Quit rates and harm reduction are also outcomes which can be used to determine the impact of the intervention and will be reported as has been observed in other studies.
^
35
^
^,^
^
36
^

In order to assess the impact of the intervention on smokers perse FEV1/FEV6 was measured. This measure is a substitute for FEV1/FVC in diagnosing airflow obstruction and may better predict COPD-related pathology and morbidity.
^
37
^ The use of 6-s expiratory maneuvers makes handheld spirometry faster and easier, provides a more explicit end-of-test definition. Its use in primary care has also been demonstrated for the detection of COPD in adults.
^
38
^

Our intention is to enhance the application of evidence in the naturally occurring clusters which are the slums. Each of the slums is a unit with similar sociodemographic features where interventions can be more effective, compliance will be better and contamination less likely. We would like to capture the population level effects of the intervention. Thus, a cluster randomisation trial was chosen.

This study aims to assess the effectiveness of a “smoke-free home” intervention in partnership with women’s self-help groups in the slums of Kochi corporation, Kerala. This is a hybrid type 2 effectiveness-implementation research
^
39
^ combining the evaluation of effectiveness of the intervention and also assessing the implementation process. We hypothesize that a tobacco smoke-free home initiative in partnership with self-help group women will be effective in significantly reducing SHS in homes and SHS exposure among women and children of those homes over a period of 1 year. The specific aims are:
•To determine the effectiveness of an intervention led by women’s self-help groups to reduce indoor tobacco smoking by measuring urinary cotinine levels and reduction in indoor smoking by measuring PM 2.5 as an indicator for tobacco smoke in the home environment.•To correlate the urinary cotinine levels with the PM 2.5 in the indoor home environment.•To measure the effect of the intervention on the FeV1/FeV6 among smokers.•To explore the impact of the intervention on quitting rate, smoking intensity through in depth interviews and focus group discussions.

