In the next two months home visits will be conducted to paste the smoke free home stickers or distribute the calendars and reinforce the message of not smoking within homes and to get widespread recognition of the movement. Based on the findings of the baseline survey customized messages to quit will be delivered. The SHG-ASHA combined will also communicate the results of the cotinine levels and 2.5pm to the household members. The cotinine levels among the children and women will be an especially powerful tool to motivate and influence men to quit smoking within the homes and then to quit ultimately. If they express an interest to quit, they will be referred to the nearest urban primary health center for tobacco cessation. The influencers will be contacted again to encourage the smoker to quit smoking within home and to quit. Creating a movement and making “not smoking within the house an acceptable sociocultural norm” is the objective. At the end of the intervention as part of the dissemination activity smoke free homes declaration meeting for all community members in the presence of political leaders will be conducted.

*Control arm*: The other arm will get the standard of care which would include the routine programs which are being run by the government as part of the national tobacco control program such as training of health and social workers, NGOs, school teachers, and enforcement officers; Information, Education, and Communication (IEC) activities; school programmes; monitoring of tobacco control laws; coordination with Panchayath Raj Institutions for village level activities; and setting-up and strengthening of cessation facilities including provision of pharmacological treatment facilities at district level. Periodic assessments will be done at 10 and 16 months.

Health workers will conduct end-line surveys soon after the intervention and six months after the intervention in the intervention and control arm with the same questionnaire, urinary cotinine measurement and SHS measurement with an environmental sensor. Thus the measurements will be at 6, 10 months and 16 months respectively.

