### Outcomes

**
*Primary and secondary*
**

The primary outcome is SHS exposure at homes at 10 months and 16 months as assessed by the change in mean urine cotinine levels among women and or children of the smoker at the individual level. The secondary outcomes will include individual level self-reports of smoking within homes, particulate matter 2.5, harm reduction (reduction in the number of cigarettes smoked), quitting of smoking, blood pressure, Fagenstrom Nicotine dependence score, and comorbidities. Individual level assessment of Fev1/Fev6 will also be carried out with handheld spirometry considering a cut off of 73% to be indicative of COPD which is also a secondary outcome. Forced expiratory volume in 1 second (FEV1) is the maximum amount of air that the subject can forcibly expel during the first second following maximal inhalation.
^
46
^ Similarly, forced expiratory volume in 6 seconds (FEV6) is the volume of forcibly exhaled air measured during 6 seconds
^
47
^ which can be measured by handheld spirometry.

Cluster level assessment of 2.5 particulate matter in homes will also be done with air quality monitors. Monitoring and assessing intervention in terms of development of a training booklet, educational material, number of meetings organized, proportion of self-help group members in the area participating and inviting local self-government members to participate.

In order to understand the reasons for success and failure, in-depth interviews of men who have successfully quit smoking within homes, quit smoking completely, ASHAs, and health workers will be conducted. Focus group discussions of wives of smokers who quit smoking within homes and those who reduced the number of cigarettes will be conducted.

*Data analysis and statistical plan*: Data will be entered electronically on a secure file storage system and password protected. Data will be anonymised by assigning a unique identification number to each smoker. Outcome data will be reported in accordance with the Standard Protocol Items: Recommendation for Intervention Trials (SPIRIT). All the smokers will be included in the analysis regardless of reduction in smoking within homes.

**
*Participant flow*
**

30 clusters will be randomly assigned into two groups and will receive intended intervention and will be analyzed for primary outcome of urinary cotinine. For each group losses and exclusion of clusters and individual participants will be recorded (
Figure 1).

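### A declaration meeting with the Mayor and press is planned before the 16-month primary assessment, leaving open a route by which publicity could reach control slums and blinded outcome collectors

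*Protocol article*

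**What the plan says.** Two places in the protocol article describe the meeting. The behavioural intervention text in Methods has: "At the end of the intervention as part of the dissemination activity smoke free homes declaration meeting for all community members", with political leaders present. The Discussion, after the RE-AIM table, widens the attendance: "At the end of the intervention, declaration meeting will be held where Mayor and other officials, elected representatives, health officials and press will attend".

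Follow-up continues after that point in both arms. The control-arm paragraph says "Health workers will conduct end-line surveys soon after the intervention and six months after the intervention in the intervention and control arm", and then "Thus the measurements will be at 6, 10 months and 16 months respectively". Under Outcomes, "The primary outcome is SHS exposure at homes at 10 months and 16 months", assessed by urine cotinine in women and/or children. The Maintenance row of Table 2 rests on the same two surveys: "In order to determine maintenance there will be an immediate survey after intervention and then another one at the end of 6 months".

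Sample selection draws all 30 clusters, for both arms, from slums and colonies of Kochi Corporation and the areas next to it. The Introduction supports cluster randomisation partly on the ground that "compliance will be better and contamination less likely". The Blinding paragraph says that those who collect outcome data will be blinded. Nothing in the article confines the meeting or its press coverage to intervention slums before month 16, or plans to record whether control households were exposed to it.

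**The concern.** A public declaration of smoke-free homes resembles the intervention itself. The Methods list endorsement by elected representatives among the community-level components, and they name a change in the social norm about smoking indoors as the objective. Controls are meant to receive only the routine government programme. The argument that contamination is unlikely works for activity that stays inside a slum. It does not cover press coverage in the city that supplies both arms.

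Two things are at stake at month 16. If control households respond to the publicity, the cotinine contrast shrinks toward no difference. If coverage names the participating slums, the health workers who do the surveys may learn the allocation. That matters most for the self-reported secondary outcomes: indoor smoking, quitting and cigarettes per day.

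A second problem is that the order of the meeting and the 10-month survey is not given, although both are placed at or soon after the end of the intervention.

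**Working it through.** **1. Timeline.** Measurements are at months 6 (baseline), 10 and 16. The Methods describe two months of home visits and then two more, so delivery ends at about 6 + 4 = month 10. The gap from there to the last survey is 16 − 10 = 6 months. The abstract instead mentions six months. If delivery ran six months from month 6, it would end at month 12, leaving 16 − 12 = 4 months. On either reading the meeting comes before a primary assessment.

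**2. The plan's own sample size.** Inputs from the sample size section: 113 per arm under individual randomisation, ICC 0.06, mean cluster size 20, CV of cluster size 0.45, 80% power, two-sided 5%, dropout 10%.
- Variance inflation = 1 + ((CV² + 1) × m − 1) × ICC = 1 + ((0.2025 + 1) × 20 − 1) × 0.06 = 2.383 (stated 2.4).
- 113 × 2.4 = 271.2 (stated 271); 271 / 20 = 13.6, so 14 clusters (stated 14).
- 271 / 0.90 gives 302 and 271 × 1.10 gives 299 (stated as rounded to 300).

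The stated figures reproduce, and the sample size is not in question here. The SD behind 113 is not given, but it is not needed below.

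**3. Illustration of dilution.** The fraction of the effect gained by controls, c, is an assumption; the documents give no such figure. The design's noncentrality is 1.960 + 0.842 = 2.80. If controls gain a fraction c, the contrast is multiplied by 1 − c, and power = Φ((1 − c) × 2.80 − 1.96).

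| Assumed c | Contrast (ng/ml) | Power, 271 analysed per arm | Power, 300 analysed per arm | Analysed per arm to keep 80%: 271/(1 − c)² |
|---|---|---|---|---|
| 0 | 0.030 | 80% | 84% | 271 |
| 10% | 0.027 | 71% | 76% | 335 |
| 20% | 0.024 | 61% | 66% | 424 |

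For the 300 column, the noncentrality is recomputed with an effective size of 300 / 2.383 per arm. These figures model gain in the control arm only.

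**4. Order relative to the 10-month survey.** For a single meeting in a given slum there are two cases.
- *Meeting first.* It is the last part of the delivered package. It may sway self-reported indoor smoking at month 10. Month 16 then measures persistence of a package that includes the meeting.
- *Survey first.* Month-10 answers are untouched, but the meeting adds exposure between the two follow-ups on which Maintenance rests.

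The article does not say which applies, or that the order will be the same in every intervention slum.

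**The case against.** The strongest reply is that the meeting belongs to the intervention. It is described within the behavioural intervention, directly after the aim of building a movement, and it is addressed to community members. On that reading month 16 properly measures persistence of the whole package. This stands for a closing meeting held within a slum. It is weaker for an event with the Mayor and press, which the Methods label dissemination.

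The second reply is that reach into control slums is inferred. Nothing says that control residents attend, that there is one city-wide event rather than one per cluster, or that coverage would be wide. The adjacent peri-urban areas need not come under the same Mayor. This stands, and it is why the point is a risk and not a finding of contamination.

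Third, the primary outcome is a laboratory measurement, so unmasking of data collectors bears mainly on secondary self-reports. That also stands.

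A reader might infer more: that the meeting both biases month-10 self-reports and renews the intervention during the maintenance period, so that month 16 no longer measures persistence. The documents do not support this. The two effects need opposite orders of meeting and survey, so one meeting cannot cause both in the same slum, and the order is not stated.

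**Conclusion.** The point holds as a cheap, specific improvement. The documents establish that a publicity event for the trial's own message is scheduled before primary data collection ends, in the area that supplies both arms, with no safeguard described. They do not establish that it would reach controls or unmask collectors, or how large either effect would be.

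The likely direction is dilution of the 16-month cotinine contrast. The drop from 80% power to about 71% or 61% rests entirely on the assumed 10% or 20% gain among controls, on a true effect equal to the planned 0.03 ng/ml, and on a normal approximation. If the meeting followed the 10-month survey, added exposure in the intervention arm would push the contrast the other way, and the net effect at month 16 could not be predicted. The unstated order is a smaller but definite gap, because it decides what the month-10 and month-16 values represent.

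**What to change.** - Hold the event with the Mayor and press, and any public release of trial results, only after the 16-month survey is complete in all 30 clusters. Returning cotinine and PM2.5 results to households, as the Methods plan, is unaffected.
- If a closing meeting is wanted at the end of the intervention, hold it within each intervention slum, without press. State whether it comes before or after that slum's 10-month survey, and keep that order the same in every intervention slum. If it comes before, describe it as part of the package.
- Bring the Methods and Discussion descriptions of the meeting into line with this, and settle the length of delivery (six months in the abstract, two plus two months in Methods) so that the end of the intervention is a defined date.

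The cost is delayed visibility for the local self-government and some loss of momentum. The Study status section says baseline collection is still under way, so the change can be made before any follow-up survey.

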## Ethics approval and consent to participate

Institutional ethical Committee approval has been obtained vide letter dated 18-10-2022 vide Institutional Ethical Committee of Amrita Institute of Medical Sciences (IEC-AIMS-2022-COMM-284). Informed consent will be taken from all participants or parents/legal guardians of minors to participate in the study.

## Data Availability

No underlying data are associated with this article. figshare: Eng Questionnaire.
https://doi.org/10.6084/m9.figshare.24468202.v1
^
26
^ This project contains the English language version of the questionnaire that will be used in the study. figshare: Questionnaire for Tobacco Smoke-Free Homes.
https://doi.org/10.6084/m9.figshare.24314530.v1
^
27
^ This project contains the original questionnaire that will be used in the study. Data are available under the terms of the
Creative Commons Attribution 4.0 International license (CC-BY 4.0).
